### Randomization

This study has a single-blind design, as far as the evaluator is concerned, since the characteristics of the treatment do not allow for double- or triple-blind experimental procedures. A randomization technique based on a single sequence of random assignments was used. A list of random numbers generated by the computer was used, and subjects were assigned a number based on their order of inclusion in the study. According to the technique described above, the 58 subjects were randomly assigned to one of the two study groups. Randomized subjects leaving the study will not be replaced, as a dropout percentage has already been considered when estimating the sample size.

### Intervention

In this study, we will facilitate two different types of support groups for a sample of caregivers.

Regarding the experimental group, the minimum number of participants will be 3 and the maximum number will be 12. This group includes 16 meetings: 1 to present the study to the participants and for administration of the questionnaire; 14 dedicated to discussions led by the facilitator, who presents topics, as described below; and a final meeting dedicated to the administration of the questionnaire.

The protocol of the psychosocial intervention includes the following topics:

First meeting—“Presentation of the participants of the group and administration of the questionnaire.” The facilitator will present the activity, the participants will introduce themselves, and the questionnaire will be administered.Second and third meetings—“Let’s get to know Alzheimer disease: what is it? Disease and epidemiology.” The facilitator will explain what Alzheimer disease is, providing theoretical information about the disease and its epidemiology. This allows caregivers to get a first complete picture of their family member’s disease.Fourth and fifth meetings—“Let’s get to know Alzheimer disease: what is it? Symptoms and phases.” The facilitator will give further theoretical information on Alzheimer disease, focusing in particular on the stages of the disease, descriptions of the stages, and the symptoms of the disease.Sixth and seventh meetings—“Our changing family member: how to relate to him/her?” The facilitator will introduce the topic concerning the changes of the ill family member due to the symptoms of dementia. In particular, the facilitator will try to focus on relational changes between the caregiver and family member, providing useful information on how to relate.Eighth and ninth meetings—“Parents and children, husband and wife: the changing family.” The facilitator will introduce the topic of changes in the family structure as a result of the Alzheimer disease event, expose what are the most common changes, and describe strategies for dealing with them.Tenth and eleventh meetings—“Being a caregiver: the changes in our lives.” The facilitator will introduce the topic of personal changes in the caregiver’s life and what can be useful to improve his or her condition. The facilitator will expose the most common changes in the caregiver’s life, focusing on the importance for the caregiver to take care of himself or herself.Twelfth and thirteenth meeting—“Let’s get to know each other better: emotions and photography.” Each participant will bring personal photos that represent his or her life as a caregiver. Through the photos, each participant will talk about his or her own caregiving experience and story.Fourteenth and fifteenth meetings—“The emotions and experiences of being a caregiver.” The facilitator will give space to the participants’ emotions centered on being a caregiver.Sixteenth meeting—Administration of the questionnaire and conclusion of the group intervention. The facilitator will collect thoughts and reflections at the end of the group and will administer the questionnaire.

Regarding the control group, the minimum number of participants will be 3 and the maximum number will be 12. This group includes 16 meetings: 1 for the presentation of the study to the participants and for the administration of the questionnaire, 14 for free discussions, and 1 final meeting for the administration of the questionnaire and conclusion of the group intervention. The control group will follow self-help methodology in such a way that the facilitator will have the sole task of facilitating communication between members of the group as the topics are chosen and treated freely by participants.

For both groups, each session will last 1.5 hours. During the first meeting for both groups, the informed consent forms with explanations about the intervention will be completed and the first questionnaires will be completed. In the final meeting, participants from both groups will complete the final questionnaire; after 6 months, they will be contacted by the researchers for the follow-up assessment.

### Outcome Measures

#### Primary Outcome

The primary outcome is caregiver burden, which will be evaluated using the Caregiver Burden Inventory scale [22]. This tool evaluates the care load, analyzing its multidimensional aspect, and was developed for caregivers of patients with Alzheimer disease and related dementias. It consists of 24 questions that are grouped into five sections representing stress-related factors: objective load (questions 1-5), evolutionary load (questions 6-10), physical load (questions 11-14), social load (questions 15-19), and emotional load (questions 20-24). Each statement is assigned a value on a 5-degree scale of increasing activity.

#### Secondary Outcomes

Secondary outcomes include coping strategy, measured using the Coping Orientation to Problems Experienced (COPE) instrument; depression, measured using the Hospital Anxiety and Depression Scale (HADS); and quality of life, measured using an ad hoc constructed questionnaire.

The COPE instrument is a self-report questionnaire that considers different coping modalities. The questionnaire consists of 60 items. The questionnaire evaluates how often the subject uses particular coping processes in difficult or stressful situations. There are four possible responses, ranging from “I usually don’t do it” to “I almost always do it.” The 15 different coping mechanisms considered by the questionnaire are as follows: activity, planning, suppression of competitive activities, containment, seeking information, seeking understanding, emotional venting, positive reinterpretation and growth, acceptance, devotion to religion, humor, denial, behavioral detachment, mental detachment, and drug or alcohol use [23].

The HADS is an instrument that measures symptoms of anxiety and depression and consists of 14 items: seven for the anxiety subscale and seven for the depression subscale. With regard to anxiety, we will focus mainly on the symptoms of generalized anxiety disorder; regarding depression, we will focus on anhedonia, the main symptom of depression. Scores range from 0 to 3 for each item. For each of the statements, the subject is asked which of four possible options best describes their emotional state [24].

The perception of quality of life will be assessed through four ad hoc items that investigate the person’s experience with respect to the quality of his or her leisure time, health status, mood, and social relationships. Each item has five possible responses, with scores ranging from 0 to 5.

In addition, a complete checklist on the demographic characteristics of the sample will be collected, with the aim of profiling the participants on the basis of their living arrangements, income, past occupational activity, family composition, age, and gender. Those background variables will be used in descriptive statistics to evaluate their influence on the study outcomes.

### Data Analysis

A descriptive analysis of the sample will be carried out through univariate and bivariate statistical analysis. Continuous variables will reported as mean and SD or median and IQR, based on their distribution, and will be evaluated using the Shapiro-Wilk test. The comparison of variables between groups at baseline will be carried out by means of unpaired Student *t* tests or Mann-Whitney *U* tests, based on their distribution. Categorical variables will be expressed as absolute frequencies and percentages, and statistical significance will be evaluated using chi-square tests or Fisher exact tests, in the case of comparisons between small subsamples.

In the second phase, the analysis of follow-up data will be carried out in order to assess the effectiveness of the intervention. This phase of analysis involves the use of multivariate statistical techniques, in particular, repeated-measures ANOVA, in order to compare changes in outcome measures over time between the intervention group and the control group. In the case of different exposure times between subjects, the Cox regression model will be employed in order to identify factors associated with the change in key endpoints. Statistical significance will be set at *P*<.05.

Every effort will be made to collect all data within the specified time frame. In the case of missing and unrecoverable data on the primary endpoints, we will assume that these events are related to chance. Analyses will be performed by applying list-wise deletion to remove cases with missing values from the final database in order to obtain unbiased estimates.

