Support groups are one of the most important interventions: people face the same problems and share their experiences through mutual help [15,17-19]. These kinds of groups provide the caregiver with a comfortable environment where they can share their emotions, reduce stress and caregiver burden, alleviate social isolation, and improve quality of life. The World Alzheimer Report 2015 reported that there is a need to strengthen services for caregivers of Alzheimer patients in order to reduce their burden by making health workers aware that caregivers are an essential part of ongoing care for the Alzheimer patient [20,21].

Following these reviews in the literature, it seems important to assess the effectiveness of group interventions in supporting the family caregiver of the person with Alzheimer disease.

The intervention described in this paper was designed and developed for the project INNovazione sociale e tecnologica per le FAMIGLIE che assistono malati affetti da Alzheimer (InnFamiglia), funded by Fondazione Cariverona. The project aimed to support older people affected by Alzheimer disease and their families throughout the duration of the disease, from initial subjective memory complaints to the severe dementia phase, overcoming the fragmentation of the services available in the local community. The project, in fact, will exploit an ecosystem of innovative services, designed in a participatory approach with the older patients, their families, and local stakeholders. The services will include the following: the development of physical and cognitive interventions, integrated with technological solutions to slow down and prevent disease progression; the availability of a daily care center for patients at the mild to moderate stages; the delivery of specialized training to a multidisciplinary team for home assistance of patients at the severe stage; and the provision of tailored interventions to support and educate informal caregivers, such as the one discussed in this paper. The study presented in this paper aims to analyze the impact of a psychosocial intervention provided to a group of informal caregivers of patients with Alzheimer disease, guided by a trained psychologist for facilitating the expression of emotional states, compared to a traditional self-help group. The factors observed and evaluated in the assessment will be the caregivers’ depression and coping strategies, caregiver burden, and their perceived quality of life.

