## Results

Participant recruitment, enrollment, and data collection began in 2021. Enrollment continued until September 2022, at which time the last group began the intervention. Data collection will be completed by December 2022, and data analysis will be completed by March 2023. The study findings will be published in peer-reviewed scientific journals and will be presented at scientific meetings. Summaries of the results will also be made available to investigators for dissemination within their clinics.

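### Both arms are treated in support groups of 3 to 12, but neither the repeated-measures ANOVA nor the sample size allows for within-group correlation; if there is any, the 5% test is anti-conservative

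*Protocol article*

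**What the plan says.** The Randomization section assigns individual caregivers to the two arms from a computer-generated list. Treatment is then given in groups. The Intervention section says, for one arm, "Regarding the experimental group, the minimum number of participants will be 3 and the maximum number will be 12" and, for the other, "Regarding the control group, the minimum number of participants will be 3 and the maximum number will be 12". Members share 16 sessions of 1.5 hours. In the control arm content may differ from one group to the next, because "the facilitator will have the sole task of facilitating communication between members of the group as the topics are chosen and treated freely by participants". The Results section confirms that groups were started in sequence: "Enrollment continued until September 2022, at which time the last group began the intervention".

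The Data Analysis section names the effectiveness analysis as multivariate techniques, "in particular, repeated-measures ANOVA, in order to compare changes in outcome measures over time between the intervention group and the control group", with significance at P<.05. The sample-size paragraph uses a two-group, two-time repeated-measures ANOVA with effect size 0.243, 90% power and a 5% level. It arrives at 48 subjects, raised to 58 (29 per arm) for dropout. Support group, ICC, design effect and random group effects are not mentioned anywhere.

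**The concern.** Individual randomisation makes caregivers independent at baseline. It does not keep them independent once they have spent four months in the same small group. A cohesive or a difficult group can move all its members in one direction, and so can the period in which it met; the Discussion itself notes that COVID-19 restrictions may affect participation and relationship-building.

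A repeated-measures ANOVA with caregivers as the independent units counts such a shared shift as several separate pieces of evidence. With as few as three groups per arm, one unusual group can carry much of the arm difference. This concerns the primary comparison, on the Caregiver Burden Inventory (CBI). At stake are the validity of P<.05, the width of the confidence interval and the claimed 90% power.

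**Working it through.** **Inputs from the protocol article.** Effect size 0.243 (read as Cohen's f), 2 groups, 2 times, alpha 0.05, power 90%, 48 evaluable, about 20% dropout, 58 enrolled as 29 per arm; groups of 3 to 12.

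**Assumed, not in the documents.** Within-person correlation ρ = 0.5; ICC of the change in burden 0.01, 0.05 or 0.10.

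**1. The plan's own figure.** Noncentral F with λ = f²·N·2/(1−ρ), df = 1 and N−2.
- N = 48: λ = 0.243² × 48 × 2/0.5 = 11.34, power 90.9%.
- N = 46: power 89.7%.
- So 48 is the smallest even N that reaches 90%. It leaves no room for a design effect.
- 48 × 1.2 = 57.6, giving 58: the only inflation is for dropout.
- The result depends on ρ: 0.3 would give 66 and 0.6 would give 38. That 0.5 reproduces 48 is the reason for using it.

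**2. Feasible group structure.** 29/12 = 2.4, so at least 3 groups per arm; 29/3 = 9.7, so at most 9. With 24 evaluable per arm, three equal groups have 8 members each, four have 6, eight have 3. Enrolment of 12/12/5 with proportional dropout leaves about 10/10/4, with effective size (100 + 100 + 16)/24 = 9.

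**3. Type I error if grouping is ignored.** Design effect DE = 1 + (m−1)·ICC; actual level ≈ 2·[1 − Φ(1.96/√DE)]. For groups of 8 at ICC 0.05, DE = 1.35, 1.96/√1.35 = 1.69, level 9.2%.

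| Group size | ICC 0.01 | ICC 0.05 | ICC 0.10 |
|---|---|---|---|
| 3 | 5.2% | 6.2% | 7.4% |
| 6 | 5.6% | 8.0% | 11.0% |
| 8 | 5.8% | 9.2% | 13.3% |

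Simulation of 40,000 null trials per setting, with a t test on change scores (equivalent to the group-by-time test with two times), agrees: for groups of 8 it gives 5.8%, 9.2% and 13.4%. At ICC 0 the test holds 5% within simulation error. The uneven 10/10/4 split gives up to about 10% at ICC 0.05 and just under 15% at ICC 0.10.

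**4. Power at N = 48, ICC 0.05.** Divide λ by DE.
- Groups of 6: DE = 1.25, λ = 9.07, power 83.8% with 46 df.
- Groups of 8: DE = 1.35, λ = 8.40, power 81.0% with 46 df.
- With degrees of freedom counted on groups: four groups per arm give 2×4 − 2 = 6 df and 71%; three per arm give 2×3 − 2 = 4 df and 59%.

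**5. How well the group variance can be estimated.** With three groups of 8 per arm, the ANOVA estimate of the between-group variance is zero or negative in about 41% of trials at ICC 0.05 and 54% at ICC 0.01.

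**The case against.** The strongest reply is that no ICC is documented and the harm could be slight. That stands as a limit on size: at ICC 0 the test is valid, and at ICC 0.01 the excess is under one percentage point for groups of 3 to 8. A reader might infer that the false-positive rate certainly exceeds 5%. The documents support only the conditional statement.

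A reader might also take the cap of 12 as the typical group and quote a type I error of 11.5% or 18%. Those figures need two full groups of 12 evaluable members per arm, whereas 29 enrolled per arm requires at least three groups.

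It may be said that a condensed article leaves the error structure to an analysis plan that is not shown. This stands in part, since a group term could be added there. But the article fixes both the method and a sample size, and the sample size reproduces with no design effect.

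Two further inferences go too far. The remark that "people face the same problems and share their experiences through mutual help" is background on support groups in general, not a stated mechanism for both arms; the Discussion credits the experimental arm's expected advantage to its structure. Nor do the documents say whether facilitators differ between groups, so a facilitator effect cannot be assumed. Shared sessions, group-chosen topics in the control arm and different start times are enough to make zero correlation doubtful.

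Lastly, the remedy is weak with few groups: a variance estimated at zero takes a mixed model most of the way back to the unadjusted analysis. That is correct and shapes the fix.

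**Conclusion.** The point holds in conditional form. The protocol names an analysis and a sample size that treat caregivers as independent, although both arms are delivered in interacting groups, with 3 to 9 groups per arm. For any positive within-group correlation of the change in burden, the planned test is anti-conservative and the claimed power is too high.

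The direction is firm. The size rests on assumed ICCs of 0.01 to 0.10, on 24 evaluable per arm and, for power, on ρ = 0.5. Over that range the inflation runs from negligible to nearly three times the nominal level. The point is worth correcting before the data are analysed because it affects the primary comparison. It does not show that the trial must be enlarged.

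**What to change.** - Record each participant's support-group identifier.
- Replace the repeated-measures ANOVA for the CBI with a linear mixed model that has a random support-group effect nested within arm on the post-baseline scores, plus within-person correlation, with Kenward-Roger or Satterthwaite degrees of freedom.
- State in advance that the group term stays in the model and is not dropped because its variance is non-significant or estimated at zero.
- Add a sensitivity analysis on support-group means, whose degrees of freedom come from the number of groups.
- Report the ICC with its confidence interval.
- Beside the sample size, state that 90% power assumes no clustering, and give the power over a plausible range of ICCs.

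The practical cost is one recorded variable and revised analysis wording. No added enrolment is needed, and the article reports that enrolment ran until September 2022. The statistical cost is larger: wider intervals and, because there are few groups, noticeably lower power. That cost belongs to the design, and the unadjusted analysis only hides it.

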## Methods

### Study Design

The study is designed as a randomized controlled trial (RCT). The RCT will include an experimental group, in which participants will undertake the psychosocial intervention, and a control group, where participants will receive support according to the traditional self-help methodology. Interventions for both groups will last 4 months and will be comprised of 16 sessions. The following evaluation phases are planned: T0 (baseline), T1 (end of treatment), and T2 (follow-up at 6 months). At each stage, a self-assessment questionnaire will be administered as described in Multimedia Appendix 1. Figure 1 describes the experimental design.

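### Cox regression is named for finding factors associated with score change, but the endpoints are questionnaire scores at set visits and no event or event time is defined

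*Protocol article*

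**What the plan says.** The second paragraph of Data Analysis gives the between-arm comparison of changes over time to repeated-measures ANOVA. It then adds a conditional analysis: "In the case of different exposure times between subjects, the Cox regression model will be employed", with the stated purpose to "identify factors associated with the change in key endpoints". The term for the trigger, exposure time, is not defined.

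The endpoints are these:

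- **Primary:** "The primary outcome is caregiver burden, which will be evaluated using the Caregiver Burden Inventory scale". The instrument has 24 items, and "Each statement is assigned a value on a 5-degree scale of increasing activity".
- **Coping:** "Secondary outcomes include coping strategy, measured using the Coping Orientation to Problems Experienced (COPE) instrument", a 60-item questionnaire.
- **Anxiety and depression:** the 14-item HADS. "Scores range from 0 to 3 for each item".
- **Quality of life:** "The perception of quality of life will be assessed through four ad hoc items".

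Study Design sets three assessments: T0, T1 and T2. "At each stage, a self-assessment questionnaire will be administered". The course has the same planned length in both arms, 4 months and 16 sessions.

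**The concern.** Cox regression relates covariates to the hazard of an event, using the time at which each person has the event or is censored. The sentence applies it to change in scores. A score change has a size and a direction but no time of occurrence, and unequal exposure between people does not give it one. Differing observation times are a reason to put time into a model for the score, not to change to a survival model.

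This matters in two ways. First, the sentence cannot be carried out as written: the analyst must first turn a score change into an event, and the article gives no rule for that. Second, any such rule changes the question. A factor associated with the hazard of crossing a threshold need not be a factor associated with the amount by which burden changes, and only the second is what the article says it wants to know.

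**Working it through.** **1. What the design is sized for.** Participants, Recruitment, and Sample Size gives an effect size of 0.243 (a 4.61-point reduction in burden), 90% power, a significance level of .05, and repeated-measures ANOVA with two groups and two measurement times. The within-person correlation ρ is not given; I assume 0.5 and show a range.

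- Noncentrality: λ = f²·N·m/(1 − ρ), with m = 2 measurement times. At N = 48: 0.243² × 48 × 2 / 0.5 = 0.05905 × 192 = 11.34.
- With 1 and 46 degrees of freedom, power is 0.909, and 48 is the smallest even total that reaches 90%. The article's figure is reproduced.
- Required N for other values of ρ: 92 (ρ = 0), 66 (ρ = 0.3), 30 (ρ = 0.7).
- Dropout allowance: 48 × 1.2 = 57.6, giving the stated 58.

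The sample size therefore rests on change in a score. The article gives no event count, hazard ratio or time-to-event power, so there is no Cox figure to reproduce.

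**2. What a Cox model needs, against what the article supplies.**

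| Needed | In the article |
|---|---|
| An event | None. No threshold or responder rule for the Caregiver Burden Inventory, COPE, HADS or the quality-of-life items |
| An event time for each person | None. Scores exist only at T0, T1 and T2 |
| A censoring rule | None |
| An outcome that is the occurrence of an event | The stated target is change in scores |

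The last row is decisive. The other three could be filled in by a fuller document, but the outcome would then no longer be the one stated.

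**3. If an event were imposed.** There are two assessments after baseline. A person who crosses a threshold is known only to have done so between T0 and T1 or between T1 and T2. All recorded event times therefore cluster at two nominal visits. They are heavily tied and interval-censored, a poor fit for a standard Cox model. The size of each change is also lost.

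**4. Could the condition be met?** I set the Results section against Study Design and Intervention.

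- The last group began in September 2022, and data collection ends by December 2022.
- A 4-month course puts its end in January 2023. Session spacing is not stated. If the 16 meetings were weekly, the last would come 15 weeks after the first, between mid-December 2022 and mid-January 2023. T1 is therefore at best borderline.
- Intervention places the follow-up contact 6 months after the final meeting, so T2 falls between about mid-June and July 2023. Even if the 6 months ran from baseline, T2 would be in March 2023.

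On either reading, T2 for the last group lies after the stated close of data collection. If those dates stand, the last group is observed for less time than earlier ones. Unequal follow-up is foreseeable, and the Cox clause is more than a remote contingency.

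**The case against.** The strongest reply is that the arm comparison does not depend on this sentence. That is correct. Data Analysis assigns that comparison to repeated-measures ANOVA, the sample size is built on the same method, and the Cox analysis has a separate purpose and a condition attached. A reader might infer, because the sentence stands in the paragraph on effectiveness, that Cox would replace the ANOVA and turn a mean difference into a hazard ratio. Nothing in the article says so.

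The second reply is that the article condenses a fuller protocol, and an event definition, time origin and censoring rule may stand there or in an analysis plan. This too is fair. A reader might infer that a cut-off would be chosen after seeing the data; the article does not show that. The reply does not remove the point, however, because the article itself names the target as change in the endpoints and pairs it with a model for something else. That is a mismatch in the text, not a missing detail.

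Third, with a prespecified threshold, tied or interval-censored times can be handled by suitable methods. That would be less efficient, not impossible. It would still answer a different question from the one stated.

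Fourth, exposure time could mean sessions attended or length of follow-up. The article does not say which. The mismatch holds under both meanings.

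**Conclusion.** The point holds in limited form. As stated, Cox regression does not estimate which factors are associated with change in the questionnaire scores. The affected part is the conditional, factor-finding analysis; the between-arm test of caregiver burden is not affected.

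No numerical loss can be derived from the document. A reader might reach for the efficiency of a median split of a normal score, 2/π ≈ 0.64, and conclude that 48 evaluable participants would act like about 31 (48 × 0.637 = 30.6). That figure belongs to a simple two-group comparison of one dichotomised score. It describes neither a Cox model over two post-baseline visits nor a search for associated factors, and 48 is the sample size of the ANOVA. It should not be used to size this defect.

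The conclusion rests on the endpoints and visits as the article describes them. That the clause may be triggered rests on the article's own dates and on reading exposure time as length of follow-up.

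**What to change.** Delete the Cox sentence. In its place, state that factors associated with change will be examined with a linear model for the scores. One suitable choice is a linear mixed model for the T1 and T2 scores, with arm, actual time since baseline, baseline score and the background variables already listed under Secondary Outcomes. Label it exploratory and say that the comparison of arms remains the repeated-measures ANOVA. The article contains no mixed model at present, so this is a new element of the plan and should be declared as such. Say also what exposure time means; if it means attendance, report sessions attended by arm as a description.

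If a time-to-event question is truly intended, prespecify the event, its time origin and the censoring rule, and use a discrete-time or interval-censored method.

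The cost is a short text change and a small amount of extra modelling work for one added model. No new data or participants are needed. The change should be made before the scores are analysed.
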